## Abstract

The population of adolescents with congenital heart disease (CHD) is growing exponentially and requires transition preparation for adult-oriented health care. Nurse-led transition programs are effective in improving CHD knowledge and self-management skills. However, many clinical programs lack the human resources needed to provide transition services. Mobile health applications have the potential to prepare transition-age youth for entering adult health care. However, there are no outcome data on the impact and effectiveness of CHD transition applications. Accordingly, in partnership with a Youth Advisory Council, we developed the MyREADY Transition CHD App (the App) designed to enhance youth CHD knowledge and self-management skills. The READYorNot CHD study is a multicenter, cluster randomized noninferiority clinical trial that is evaluating the efficacy of the App plus limited nurse teaching (intervention), vs comprehensive nurse-only teaching (control) for 16- to 17-year-olds with moderate or complex CHD. Participants are being enrolled in clusters based on week of attendance in the pediatric cardiology clinic, with a 1:1 allocation between intervention vs control and target recruitment of 204 participants. The primary outcome is the change in Transition Readiness Assessment Questionnaire score from baseline to 18 months. Secondary outcomes are change in CHD knowledge score, self-efficacy, and time to first adult CHD appointment. Semistructured interviews will provide additional insights into the advantages and disadvantages of the App vs nurse-only teaching. This study will inform patients, pediatric cardiology programs, and policy makers in judging whether this mobile health intervention warrants widespread availability in clinical settings to improve transition outcomes of adolescents with CHD. Clinical Trial Registration: NCT04463446.

The number of adults with congenital heart disease (CHD) now significantly exceeds the number of children, reflecting decades of success in pediatric CHD care.^1^ This survivor population has complex needs requiring lifelong specialized CHD follow-up. Accordingly, preparing youth for the transition from pediatric to adult CHD (ACHD) care has become a major focus in the past decade. Numerous guidelines and position statements have been published to promote improved quality of care in transition processes.^2^, ^3^, ^4^ However, there remains a paucity of outcome data regarding the impact and effectiveness of CHD transition interventions. Furthermore, early adulthood is a life stage associated with lapses in care,^5^ reflecting a failure of transition preparation. Indeed, there is a lack of high-quality transition outcome data for pediatric-onset chronic health conditions.

Our team previously designed and conducted the **C**ongenital **H**eart **A**dolescents **P**articipating in **T**ransition **E**valuation **R**esearch (CHAPTER 1) study,^6^ followed by the CHAPTER 2^7^ and 3^8^ studies; these trials evaluated nurse-led transition education interventions, focusing on CHD knowledge^6^, ^7^, ^8^ and self-management skills^7^ among adolescents. These studies demonstrated that nurse-led teaching significantly improves patients’ knowledge of their CHD and self-management skills. However, nurse-led transition teaching is resource-intensive, requiring nursing time and expertise as well as space in clinical settings that may not be readily available. Nurse-led teaching may also be less accessible to patients living remote from cardiac centers, as increased distance between home and hospital has been associated with lapses in care.^9^ Furthermore, patients living in remote communities are more likely to be Indigenous^10^ and of lower socioeconomic status^11^ and may face financial barriers to attending in-person visits.^12^ Mobile health applications (apps) have the potential to mitigate some of these barriers and provide a more convenient resource to young adults as they enter adult care. Accordingly, the current study was designed to build on our experience with the CHAPTER studies by replicating the content of nurse-led teaching into an app that is youth-oriented and youth-informed.

The objectives of the READYorNot CHD study are to compare the impact of a smartphone app combined with limited nurse teaching, vs comprehensive nurse-only transition teaching, on transition readiness, CHD knowledge, self-efficacy, and time to ACHD care among youth graduating from pediatric cardiology programs. We hypothesize that the MyREADY Transition CHD App (the App) will not be significantly worse than the standard of care (ie, comprehensive nurse-only teaching) with respect to transition readiness, CHD knowledge, self-efficacy scores, and time to first ACHD clinic appointment. Semistructured interviews of participants in both groups will provide additional insights into the acceptability and merits of the App vs nurse-only preparation. This article will describe the methods of the proposed study.

## Methods

### Study design

The READYorNot CHD study is a multicenter, cluster randomized controlled trial comparing access to the App plus limited nurse teaching (intervention group), vs standard-of care comprehensive nurse-only transition teaching (control group) in a 1:1 allocation ratio. The study is registered with Clinical Trials.gov (NCT04463446) and is being conducted in accordance with CONSORT (Consolidated Standards of Reporting Trials) guidelines (Fig. 1).

**Figure 1 fig1:**
[figure not shown]
CONSORT (Consolidated Standards of Reporting Trials) diagram.

### Study setting and participants

The study is being conducted at the Stollery Children’s Hospital (Edmonton, Canada), the Hospital for Sick Children (“SickKids,” Toronto, Canada), British Columbia Children’s Hospital (Vancouver, Canada), and the Centre Hospitalier Universitaire Sainte-Justine (Montreal, Canada). These are the largest pediatric cardiology programs in Canada and offer the full range of cardiology and cardiovascular surgical services. Inclusion criteria are 16- to 17-year-olds with moderate or complex CHD (as previously defined)^13^ who have not yet transferred to adult care. Although transition interventions should begin typically by 12 years of age,^2^^,^^3^ we chose to focus on older adolescents. Transition interventions need to be consistent with the developmental stage of participants, and it is not practical to develop an app that addresses the needs of the full range of typical 12- to 17-year-olds. Furthermore, it would be difficult to conduct a study that compares 2 transition interventions spanning 5-6 years each (ie, from ages 12 to 17 years). Exclusion criteria are (1) less than a grade 6 level of reading and comprehension, based on medical records review or parent report, or (2) a history of heart transplantation, as this results in distinct health challenges. To prevent selection bias and allow study participation for those of low socioeconomic status, the absence of technology literacy or access to a smartphone and/or computer or tablet is not an exclusion criterion. Participants in the App group who do not have technology access will be provided with a cell phone and a basic data plan to allow study participation. Individual participant timelines are illustrated in Figure 2. Transfer to adult care typically occurs at age 17 or 18 years at the participating centers.

**Figure 2 fig2:**
[figure not shown]
Individual participant timeline. CHD, congenital heart disease; CRF, case report form.

### App development

The App was modified from the pre-existing MyREADY Transition BBD App,^14^ developed for youth with brain-based disabilities (BBD) by a Canadian team including coauthors ([name], [name], [name]).^15^ The BBD version of the App was developed in conjunction with a Patient and Family Advisory Council. Modifications to the BBD app to make it suitable for a CHD audience were led by a pediatric cardiologist ([name]), an ACHD cardiologist ([name]), a CHD psychologist ([name]), an information technology (IT) expert ([name]), and a Youth Advisory Council comprising 5 adolescents and young adults living with CHD. The Youth Advisory Council members were patients at 3 of the 4 participating sites and included both male and female patients. They met 3 times by video conference to provide feedback about the App; these meetings were facilitated by team members having experience leading young adult focus groups (GD, BA). Council members also provided feedback by email. Feedback addressed both the functionality and the content of the App. The council developed a list of frequently asked questions, which were included in the App, and advised on the format of video testimonials included in the App. Two Youth Advisory Council members took up roles as actors with lived experience of CHD, appearing in videos included in the App.

The App is compatible with iOS and Android phones, tablets, and computers and is available in both English and French. It has 20 modules (Fig. 3), each taking 10-15 minutes to complete. Content of the App includes but is not limited to (1) an introduction and definition of “transition” and “transfer,” (2) information about types of CHD, (3) a portable health summary with fields that participants can complete (SmartHeart Pass), and (4) tips on self-management and self-advocacy, including managing medications, making appointments, decision-making, and preparing for an elective hospital stay.

**Figure 3 fig3:**
[figure not shown]
Content of the MyREADY Transition CHD App. CHD, congenital heart disease.

The App includes games, trophies, interactive quizzes, a “customizable mentor,” and other features meant to entertain and engage adolescents. There are 51 quizzes (true/false, multiple-choice answer formats) and 10 different types of games, including puzzles, “hangman”-style games, and find-the-object challenges. The mentor is a virtual “companion” that guides them through the App. The customizable nature of the App acknowledges diversity, as users can select a mentor that mirrors their preferences or own physical appearance. The mentor also has customizable accessories, with new ones unlocked as rewards for completing sessions. The time required for games, interactive quizzes, and customizing the mentor is integrated into the session content and included within the 10-15 minutes per module. However, users earn coins that they can spend on additional games in an arcade (game room) between sessions, if they wish. These optional games are not part of the curriculum.

The App content has been designed to reflect what our team has previously included in nurse-only teaching to enable a comparison between the *mode* of transition intervention rather than the *content* of the interventions.

### Intervention group (App + limited nurse time)

Participants in the App group meet once with a registered nurse (RN) during a regularly scheduled clinic visit, or in a virtual meeting if preferred by the participant, to (1) view an introductory video about the App, (2) download the App from the Apple or Android app store, (3) obtain a unique access code, (4) set up a password, (5) ensure that they can view the App, (6) receive information about how to obtain technical support, (7) learn about their cardiac anatomy and prior surgical and/or catheter interventions with the help of a diagram ± a heart model, and (8) review 3 potential future cardiac complications, as the App is not designed to provide information about a unique individual’s CHD. A checklist is used to ensure that all topics are discussed and App-related tasks completed. This checklist is an external metric being used for nurse documentation to make sure that all steps are completed, and not one that exists in the App. Participants are encouraged to complete 2-3 modules per week and all 20 modules within 3 months of enrollment; however, they have 18 months of access to the App. Participants in the intervention group will not have access to a cardiology nurse for transition teaching after the initial session.

### Control group (comprehensive nurse-only teaching)

Participants in the control group meet with an RN who is experienced working with teens for a single one-on-one session scheduled either during a routine cardiology clinic visit, or at an alternative time depending on the participant’s preference. If done on another date, the option of a virtual meeting is provided. Sessions are youth-oriented, interactive, and engaging. A PowerPoint presentation is used to facilitate teaching and ensure that all topics are covered. Teaching is conducted in either English or French, depending on the participant’s preference. Control group participants are not provided an access code to the App. Table 1 summarizes topics covered in both groups. An optional follow-up “refresher” teaching session is provided at the following cardiology clinic appointment (usually 12-24 months later) if desired by the participant.

**Table 1 tbl1:** Content and mode of delivery of the intervention and control groups

No.	Content	Intervention group	Control group
1	Introduction to transition and its importance	App	RN
2	Provide handout of normal heart and explain blood flow and structures in simple terms	RN	RN
3	Diagram of the participant’s cardiac anatomy, including prior interventions and 3 potential future complications	RN	RN
4	Creation of a portable health summary, including name of CHD, prior cardiac interventions, and health care provider contact information	App	RN
5	Discussion of 3 potential future cardiac complications that are diagnosis specific and individualized	RN	RN
6	Medication management	App	RN
7	Discuss the concept of self-management	App	RN
8	3-sentence summary	App	RN
9	Mental health challenges—normalize and destigmatize	App	RN
10	Share resources∗	RN	RN

App and RN (registered nurse) refer to mode of delivery.

CHD, congenital heart disease.

∗ iHeartChange CHD transition website (iheartchange.org), Canadian Congenital Heart Alliance, Adult Congenital Heart Association, Vaping and Teens handout, Kids Help Phone website, and local mental health supports.

For participants in both groups, the RN reviews the participant’s medical record immediately before teaching sessions to become familiar with their cardiac history including CHD diagnoses, names and dates of cardiac surgical procedures and cardiac catheterizations, and current cardiac medications and doses.

### Group allocation

Participants are randomized by clusters defined by week of attendance in the pediatric cardiology clinic. As “week,” not study participant, is the unit of randomization, this is a cluster randomization design. This method of randomization (1) prevents 2 adolescents in the same waiting room being allocated to different groups and (2) facilitates scheduling of study RNs who are available at short notice to meet with participants. Cardiologists are not informed of group assignment, preventing potential bias by cardiologist cointervention. There is a 1:1 allocation of intervention:control weeks, stratified by site, using permuted blocks of randomly varying sizes of 2 and 4. We anticipate enrollment of 0-2 patients per week, that is, cluster size will be ≤2. To determine which weeks are intervention weeks vs control weeks, a biostatistician prepared a randomization sequence that is unique for each site. Allocation tables were locked and sent under password protection directly to a coordinator at each site.

### Treatment fidelity and quality assurance

Consistency between study RNs is a priority of this study for both the intervention and control groups. Team education has included virtual training meetings for study RNs affiliated with the intervention and control groups, held separately to avoid contamination of the intervention group or vice versa.

For both the intervention and control groups, the RN completes a checklist to document completion of each component as described in Table 1. Checklists are reviewed by team members ([name], RNs) as part of ongoing quality assurance.

Audio recordings of sessions with study participants in the control group are conducted if the participant agrees. Evaluation of treatment fidelity is based on the review of nursing checklists and/or audiotapes by the lead author.

### Protecting against sources of bias

Participants, their parents, and the study RNs are aware of group allocation as blinding is not feasible. However, clinic support staff and pediatric cardiologists are not informed of group allocation. Participants are unaware of the primary and secondary outcomes and therefore unable to consciously influence the study findings.

### Primary outcome

The primary outcome is the change in the Transition Readiness Assessment Questionnaire version 5.0 (TRAQ) score, between baseline and 18 months. The TRAQ is the most rigorous transition readiness scale for adolescents.^16^ This 20-item scale has 5 subscales (Appointment Keeping, Tracking Health Issues, Managing Medications, Talking with Providers, and Managing Daily Activities). The overall scale has high reliability (Cronbach’s α 0.94). Item and mean scores range from 1 (low) to 5 (optimal).^17^ The TRAQ has a grade 5.7 reading level and takes approximately 5 minutes to complete. We have not observed a ceiling effect; the mean self-management score at baseline in the CHAPTER 2 study (16- to 17-year-olds) was 2.9 ± 0.8.^7^ All baseline questionnaires are completed in the cardiology clinic before meeting with a study RN.

### Secondary outcomes

Given the complex, multidimensional nature of the transition process, transition interventions must consider multiple outcomes. Therefore, several secondary outcomes are planned.(1)Change in MyHeart scores between baseline, 1, 6, 12, and 18 months. The MyHeart scale (Supplemental Appendix S1) consists of 8 questions that assess participants’ knowledge of their cardiac condition. It is written at a grade 4.6 level and takes approximately 5 minutes to complete. MyHeart scores increase following nurse-only teaching.^6^, ^7^, ^8^(2)Change in General Self-Efficacy (GSE) score^18^^,^^19^ between baseline and 18 months. The GSE is a 10-item questionnaire using a 4-point Likert scale that takes approximately 2 minutes to complete. Adolescents’ GSE scores predict multiple quality of life domains, including emotional, physical, and social.^19^ Team member [name] showed that among adults with CHD, lower GSE scores were associated with being female, unemployed, and having poorer functional class.^20^ [name] and [name] documented GSE scores in adolescents with moderate or complex CHD (n = 82); mean scores were 3.0 ± 0.6.^21^(3)Excess time between pediatric and ACHD care, defined as the time interval in months between the final pediatric visit and the first adult visit, minus the recommended time interval between these visits. The “recommended time” interval was the interval suggested by the cardiologist at the final pediatric visit. For example, if the time between the final pediatric visit and first adult visit was 20 months but the pediatric cardiologist recommended 12 months, the excess time would be 8 months. Participants who have not attended the adult clinic by the end of the study period (ie, are “censored”) will still contribute to this outcome as survival analysis is designed to accommodate censored data. If the first ACHD visit takes place before the recommended time, the excess time will be zero. For the rare study participant not having a documented “recommended time,” recommendations for frequency of care will be taken from published guidelines.^22^^,^^23^ Our team has previously demonstrated the benefit of nurse-only teaching on this outcome measure.^7^(4)Semistructured interviews of participants in both study arms are currently being conducted to understand participants’ experiences. For participants in the App group, additional inquiry is seeking a deeper understanding of the App’s usability and acceptability and its impact on quantitative outcomes. Interviews are conducted once, between 3 and 6 months after enrollment. Purposive sampling^24^ is used to ensure that participants in both arms of the study are selected, with representation of all 4 participating sites. Participants are invited to participate in a 30-minute semistructured interview by phone or video call. We anticipate conducting interviews with approximately 10 participants per study arm or until data saturation has been achieved and no new themes emerge. Interviewers are experienced, independent of intervention delivery, and follow a semistructured interview guide to ensure consistency (Supplemental Appendix S2). Participants in the App group are sent screenshots from the App as an optional review before or during the interview to remind them of specific aspects of the App (quizzes, puzzles, etc) that they will be asked about during the interview.

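### The excess-time outcome starts its clock at the final pediatric visit, which for some participants comes after randomization; co-report an analysis timed from enrolment

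*Protocol article*

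**What the plan says.** All references are to the protocol article.

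- **Definition (Secondary outcomes, item 3).** Excess time is "the time interval in months between the final pediatric visit and the first adult visit", less a recommended interval. On that interval: "The “recommended time” interval was the interval suggested by the cardiologist at the final pediatric visit". There is a floor: "If the first ACHD visit takes place before the recommended time, the excess time will be zero". Follow-up may be incomplete: "Participants who have not attended the adult clinic by the end of the study period (ie, are “censored”) will still contribute to this outcome".
- **Time of randomization (Group allocation).** "Participants are randomized by clusters defined by week of attendance in the pediatric cardiology clinic". Under Study setting and participants, those enrolled are aged 16 to 17 and have not yet transferred.
- **What follows enrolment.** "Transfer to adult care typically occurs at age 17 or 18 years at the participating centers" (Study setting and participants). The optional control-group refresher is placed at "the following cardiology clinic appointment (usually 12-24 months later") (Control group).
- **Name of the outcome.** The hypothesis paragraph that closes the introduction speaks of "time to first ACHD clinic appointment", and the abstract uses nearly the same label.
- **Data collection (Measurement of outcomes at follow-up).** The first ACHD visit is sought in the medical record 18 months after enrolment, and again at study closeout if it has not yet happened.

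**The concern.** Randomization makes the arms comparable from enrolment onward. A clock that starts later, at an event the participant's own behaviour can move, does not carry that protection in full. Here the start is whichever pediatric visit turns out to be the last. Attendance is something the teaching aims at: Appointment Keeping is a TRAQ subscale, and the App covers making appointments. The arms also differ in what awaits them at the next visit. Controls are offered a refresher, while App participants have no further nurse access for transition teaching. Under Potential limitations, clinics try to rebook patients who miss appointments, and a late rebooked pediatric visit restarts the clock.

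At stake is whether a between-arm difference in this secondary outcome, or the lack of one, reflects time to adult care or only which clinic ended a delay. A reader who goes by the label in the abstract would expect the former.

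**Working it through.** **1. The article's own figures.** Its worked example is 20 months observed and 12 recommended, so excess = max(0, 20 − 12) = 8 months. This reproduces. The sample size rests on TRAQ alone and also reproduces: 64 per group (t-based, margin 0.40, SD 0.8, one-sided 0.025, power 80.1%). The design effect is 1 + (2 − 1) × 0.1 = 1.1; 64 × 1.1 = 70.4, rounded up to 71; 71 / 0.70 = 101.4, rounded up to 102; total 204. Nothing below changes it.

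**2. A short case.** Two participants are told at enrolment to return in 12 months, and both are next seen at month 22, so each is 22 − 12 = 10 months late.

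- Next seen in pediatrics, then on time for adult care: excess = 0.
- Next seen in adult care, so the enrolment visit was the final pediatric visit: excess = 22 − 0 − 12 = 10.

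**3. Same first adult visit.** Assumed plan at enrolment (month 0): pediatric visit at month 12, adult visit 12 months after that (month 24). Each participant loses 12 months and first attends adult care at month 36.

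| | A: returns late to pediatrics | B: does not return to pediatrics |
|---|---|---|
| Final pediatric visit | month 24 | month 0 (enrolment) |
| Interval recommended there | 12 | 12 |
| First adult visit | month 36 | month 36 |
| Excess as defined | max(0, 36 − 24 − 12) = 0 | max(0, 36 − 0 − 12) = 24 |
| Delay against the plan at enrolment | 36 − 24 = 12 | 36 − 24 = 12 |
| Time from enrolment to adult care | 36 | 36 |

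B's score applies the definition literally: the interval subtracted is the one given at enrolment, although that was advice to return to pediatrics.

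**4. Arm level (all rates assumed; the article gives none).** Let p be the share of an arm that lapses as in step 3, and r the share of lapsers who return late to pediatrics. Under the definition a returning lapser adds 0 months to the arm mean and a non-returning lapser adds 24. Timed from enrolment, either adds 12. Any further adult delay that is alike in both arms cancels.

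- Difference as defined, with the same r in both arms = (p_App − p_control) × 24 × (1 − r)
- Difference timed from enrolment = (p_App − p_control) × 12

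With p = 0.10 in control and 0.30 in the App arm:

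| r | As defined | From enrolment |
|---|---|---|
| 100% | 0.20 × 24 × 0 = 0.0 | 0.20 × 12 = 2.4 |
| 50% | 0.20 × 24 × 0.5 = 2.4 | 2.4 |
| 0% | 0.20 × 24 × 1 = 4.8 | 2.4 |

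With equal p and equal r, both differences are 0. With equal p = 0.10 but r = 100% in one arm and 0% in the other, the definition gives 0.10 × 24 = 2.4 months where the enrolment clock gives 0. The sign depends on which arm has the lower r.

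**The case against.** The strongest reply is that the outcome does what its name says. It is called excess time between pediatric and ACHD care, which is the transfer gap. On that reading the first participant in step 2 has no gap at transfer and the second does, so 0 and 10 are the intended scores. The stated objectives list time to ACHD care, not lapses within pediatric care, and the introduction mentions lapses only as background. The team used this measure in its earlier trial and reports a benefit of nurse-only teaching on it. That is the article's only support for the control's effect on this outcome, and a replacement measure would lack it. This stands, and it is why the definition should be kept.

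It is also true that bias between arms requires a difference in pediatric attendance after enrolment. Clinic support staff and cardiologists are not informed of allocation, so recall of missed appointments should not be driven by arm. This lessens one route to a difference. It does not remove the participants' own behaviour, which the teaching is meant to change.

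Finally, handling of participants who skip their remaining pediatric visits may be set out in a fuller protocol or analysis plan that is not shown. Its absence from the article is not held against the trial. The clock start, however, is fixed in the article itself, as is the different label in the abstract and hypothesis.

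**Conclusion.** The point holds in a limited form. The clock for secondary outcome 3 has no common start relative to randomization, so this comparison is not fully protected by it, and the quantity defined is not the one named in the abstract and hypothesis. Whether this matters in practice depends on post-enrolment pediatric attendance by arm, which the article does not report. The months in the working illustrate the mechanism under assumed rates and do not estimate a bias.

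Two stronger readings are tempting and are not supported.

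- **That the definition favours a finding of noninferiority.** A reader might infer this because late returns to pediatrics hide a delay. Step 4 shows that the same definition can shrink, match or enlarge a true difference (0.0, 2.4 or 4.8 months against 2.4). The article says that clinics try to rebook missed visits but not how often this succeeds.
- **That a known share of participants is affected.** Any such share would rest on an assumed age distribution at enrolment, age at transfer and visit interval. It would also count participants with another visit due, not those who lapse, and would say nothing about a difference between arms.

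The primary outcome and the 204 participants are untouched.

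**What to change.** Keep excess time as defined. Beside it, co-report a survival analysis of time from enrolment (randomization) to first ACHD visit, adjusted for age at enrolment and censored at study closeout for those not yet seen. State in the abstract and hypothesis which of the two quantities each statement refers to.

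The first ACHD visit is already sought at the 18-month record review and at closeout, and the enrolment date is known, so no new data are needed. The cost is one extra analysis and a few lines of wording. Its drawback is that the time scale depends partly on age at enrolment, hence the adjustment, and that it does not subtract the recommended interval. It should therefore be read alongside the current outcome and not in its place. Summing the excess over every recommended interval since enrolment would be a further option. It is more debatable, because it adds pediatric attendance to a transfer outcome and assumes that every intermediate recommendation can be found in the record.
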